### 2.3. Participants—Recruitment

For this study, female donors participating in a donor/recipient program will be recruited following a detailed explanation of the study protocol. The selection will be based on the eligibility criteria. All participants will sign a written informed consent before entering the trial. The women will be divided into two groups, i.e., group 1 (study) and group 2 (control). The allocation of patients will be achieved using a 1:1 proportional pattern, depending on the random order in which they enter each Unit. Notably, both patients and gynecologists will be aware of the study protocol used.

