### 2.4. Interventions

#### 2.4.1. Controlled Ovarian Hyperstimulation

All women will undergo ovarian stimulation with urinary FSH (Meriofert, IBSA Pharmaceutici, Lodi, Italy) starting on day 2 of the cycle. The starting dose of FSH will be 300 IU s.c. for the first 4 days adjusted thereafter according to the ovarian response. Monitoring of treatment will be performed via the measurement of serum estradiol concentrations and transvaginal ultrasound scans of the ovaries. Triggering of final follicle/oocyte maturation will be performed via the injection of a GnRH agonist at the single dose of 200 µg s.c. when at least 3 follicles greater than 17 mm in diameter are seen via ultrasound. Women in group 1 will receive only FSH, while women in group 2 will additionally receive a GnRH antagonist from day 6 of FSH treatment at a dose of 0.25 mg per day until the triggering day. The GnRH antagonist in group 2 will be injected each time immediately after the injection of FSH. Monitoring via ultrasound scans will begin on cycle day 7 and continue every day or every other day, depending on the examiner’s evaluation. In every scan, all follicles >10 mm in diameter (mean of two dimensions) will be recorded. From all women (both groups), blood samples (5 mL) will be obtained before the FSH injection (between 08.00 and 09.00 h) on cycle days 2 and 7 and then every other day. The last blood sample will be taken on the day of triggering regardless of the sampling frequency adopted. All blood samples will be centrifuged, and an aliquot will be stored at −20° until assayed.

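### The arm is fixed by open order of entry, although treatment does not differ until cycle day 7; dose decisions, withdrawals and progesterone readings that the antagonist cannot have affected are therefore analysed by a knowable arm

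*Protocol article*

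**What the plan says.** **Allocation.** Section 2.3 allocates donors 1:1, "depending on the random order in which they enter each Unit". It adds that "both patients and gynecologists will be aware of the study protocol used".

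**Treatment up to the point of divergence.** Section 2.4.1 starts FSH in every donor "starting on day 2 of the cycle". The dose is "300 IU s.c. for the first 4 days adjusted thereafter according to the ovarian response". Group 2 will "additionally receive a GnRH antagonist from day 6 of FSH treatment", each antagonist injection following directly on the FSH injection.

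**Measurements.** "Monitoring via ultrasound scans will begin on cycle day 7". Blood is taken before the FSH injection on cycle days 2 and 7, then every other day, with a last sample on the day of triggering.

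**Outcomes and analysis.** Section 2.5 counts LH peaks (10 IU/L or more) while the antagonist is being given, but progesterone above 1 ng/mL at any point in stimulation. The Abstract ties both to the antagonist period. Total FSH dose is itself a prespecified outcome (Section 2.5). Section 2.7 applies intention to treat (ITT) throughout.

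**The concern.** The point is when the arm becomes fixed and knowable. A comparison is cleanest when allocation sits immediately before the treatments part. Here it sits at entry to the Unit, and for several days nothing distinguishes the arms except that donor and clinician know, or can work out, which one applies.

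Three things can happen in that interval:

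- The FSH dose can be adjusted with the arm known.
- A donor can withdraw, possibly because she knows she will receive no LH protection.
- A progesterone reading can already be above the threshold and be credited to an arm.

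The Discussion says that the investigators met widespread fear of premature surges and ovulation when approaching IVF centres, so behaviour that differs by arm is not far-fetched. Under ITT, losses and events from this interval stay in the comparison. If they are equal between arms they pull the arms together, which favours a non-inferiority reading. If they are unequal they can push the result either way.

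**Working it through.** **1. Day count (Section 2.4.1).** FSH day 1 is cycle day 2, so FSH day k is cycle day k + 1.

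| FSH day | Cycle day | What may differ by arm |
|---|---|---|
| 1–4 | 2–5 | Nothing; dose fixed |
| 5 | 6 | FSH dose may be adjusted; no planned scan or blood sample yet |
| 6 | 7 | Blood sample, first scan and FSH decision; then the first antagonist dose in group 2 |

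Of the five FSH injections before cycle day 7, only one (FSH day 5) is adjustable. The day 7 FSH decision is the second that can be made with the arm known before the antagonist has acted.

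**2. Which samples precede the antagonist.** Blood is drawn before FSH, and the antagonist follows FSH. The day 2 and day 7 samples are therefore free of antagonist in both arms, and nothing is sampled between them.

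- Progesterone: on the Section 2.5 wording a day 7 elevation counts, and so does day 2 if that sample is taken to lie within stimulation.
- LH: no peak can be recorded between days 2 and 7. Only the day 7 pre-dose sample is in doubt.

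**3. The plan's own figure (Section 2.6).** Inputs: 20% versus 15%, margin 10 points, one-sided 5%, power 80%.

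n per group = (1.645 + 0.842)² × (0.15 × 0.85 + 0.20 × 0.80) / (0.10 + 0.05)² = 6.183 × 0.2875 / 0.0225 ≈ 79

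That is 158 in total, against 160 stated, so the figure is reproduced. Power at 80 per group is 80.4%.

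**4. Equal early loss.** The share d lost before cycle day 7 is not in the documents; 5–20% is an assumed range. Scoring the lost women as no event is also an assumption. The true rates are set at the margin, 20% versus 10%.

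- Apparent difference = 10 × (1 − d) points.
- Non-inferiority error at 80 per group = Φ(0.10d / SE − 1.645), with SE from the diluted rates. For d = 0.10, SE = √[(0.18 × 0.82 + 0.09 × 0.91) / 80] = 0.0536, so Φ(0.187 − 1.645) = 7.2%.

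| d | Apparent deficit (points) | One-sided error | Power if the lost are excluded instead (20% v 15%) |
|---|---|---|---|
| 0 | 10.0 | 5.0% | 80.4% |
| 5% | 9.5 | 6.0% | 78.6% |
| 10% | 9.0 | 7.2% | 76.7% |
| 20% | 8.0 | 10.5% | 72.3% |

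The factor (1 − d) also applies to progesterone if a share d in each arm is already elevated before the antagonist starts, because those women count as events in both arms.

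**5. Unequal early loss (assumed 15% versus 5%, both true rates 20%).** 0.20 × 0.85 = 17% against 0.20 × 0.95 = 19%: a spurious 2-point difference.

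**6. Pilot (25 per arm, Section 2.6).** One woman is 1/25 = 4 points. Two more early withdrawals in one arm than in the other make an 8-point gap in the share evaluable.

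**7. Starters needed if allocation moves to day 7.** 50/(1 − d) gives 53, 56 or 63 for d = 5, 10 or 20%. For 80 per group, 2 × 80/(1 − d), rounded up per arm, gives 170, 178 or 200.

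**The case against.** **The early dosing window is narrow.** A reader might infer that open early dosing confounds total FSH dose, oocyte yield and LH peaks. The documents do not support that: one injection, plus the day 7 decision, is adjustable before the arms part. Dosing and triggering after day 7 are open-label whenever allocation takes place. This stands.

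**Early LH peaks are largely outside the outcome.** A reader might infer that LH peaks before day 7 are counted by arm. The LH window is antagonist administration and no sample falls between days 2 and 7, so this too stands, apart from the day 7 pre-dose sample. For progesterone the objection holds only on the Abstract's wording. Section 2.5 says otherwise, and the Discussion applies the cut-off to cycles with an LH peak.

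**Early loss may be negligible.** These are healthy donors with normal ovarian reserve; poor responders and women with polycystic ovary syndrome are excluded (Section 2.2). No scan or blood sample between days 2 and 7 would prompt a cancellation. Losses of 10–20% are illustrations, and the error rates in the working rest on them and on a scoring rule that Section 2.7 does not state.

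**Moving the date alone does not cure it.** An entry-order rule applied on day 7 can be foreseen from day 2. This is correct, so the fix must include concealment.

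**The study calls itself observational and promises no definite conclusion.** That limits the stakes. But the plan assigns arms 1:1, applies ITT and tests non-inferiority, and the pilot is meant to prepare a randomised trial. Admitting bias is no reason to keep a part that is cheap to remove.

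**Allocation at enrolment is common, and the article does not state when the arm is disclosed.** Both are true. The point rests on the stated entry-order rule, which makes the arm knowable at entry.

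**Conclusion.** The point holds as a modest and inexpensive improvement. Two dose decisions, any early withdrawal, and progesterone readings on day 2 and pre-dose on day 7 fall under a knowable arm and, where they count, enter an ITT comparison, although the antagonist cannot have influenced them. For LH the exposure is at most one sample.

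The size cannot be fixed from the documents. On the assumed 5–20% early loss, scored as no event, a true 10-point deficit reads as 9.5 to 8.0 points, and the one-sided error at 80 per group rises from 5.0% to between 6.0% and 10.5%. With little early loss the effect is close to nil. The open dose decisions and the progesterone window do not depend on loss.

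A reader might also see a flat contradiction between response-based adjustment after four days and first monitoring on cycle day 7. The text permits an adjustment on FSH day 5 but does not require one, so this is a wording matter to reconcile.

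**What to change.** 1. Obtain consent to either arm, then start FSH in all donors as planned.
2. Assign the arm on cycle day 7 from a random sequence concealed until then, not by order of entry. Do so after the blood sample, the scan and that day's FSH decision are recorded, and before the first antagonist dose would be due.
3. Define the ITT set as the donors allocated at that point.
4. Treat day 2 and day 7 pre-dose LH and progesterone as baseline, and count LH peaks and progesterone elevations only from later samples, with the same wording in the Abstract and Section 2.5. This step is worthwhile even if allocation stays at entry; the day 7 values would then precede the antagonist but not the allocation.
5. Separately, reconcile the Section 2.4.1 statements on response-based adjustment after four days and on the first scan and first on-treatment blood sample on cycle day 7.

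**Cost.** Protocol and consent wording, antagonist in stock at each recruiting Unit on day 7, and slightly more starters than allocated donors (about 56 to allocate 50 at an assumed 10% loss). No visit or sample is added, because the day 7 scan and blood draw are already planned for everyone. A concealed random sequence would in effect make the pilot randomised, a step that the Discussion reserves for later; if the sponsor does not want that yet, step 4 can be adopted alone. None of this removes open-label influence on dosing and triggering after day 7.

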### 2.4. Interventions

#### 2.4.1. Controlled Ovarian Hyperstimulation

All women will undergo ovarian stimulation with urinary FSH (Meriofert, IBSA Pharmaceutici, Lodi, Italy) starting on day 2 of the cycle. The starting dose of FSH will be 300 IU s.c. for the first 4 days adjusted thereafter according to the ovarian response. Monitoring of treatment will be performed via the measurement of serum estradiol concentrations and transvaginal ultrasound scans of the ovaries. Triggering of final follicle/oocyte maturation will be performed via the injection of a GnRH agonist at the single dose of 200 µg s.c. when at least 3 follicles greater than 17 mm in diameter are seen via ultrasound. Women in group 1 will receive only FSH, while women in group 2 will additionally receive a GnRH antagonist from day 6 of FSH treatment at a dose of 0.25 mg per day until the triggering day. The GnRH antagonist in group 2 will be injected each time immediately after the injection of FSH. Monitoring via ultrasound scans will begin on cycle day 7 and continue every day or every other day, depending on the examiner’s evaluation. In every scan, all follicles >10 mm in diameter (mean of two dimensions) will be recorded. From all women (both groups), blood samples (5 mL) will be obtained before the FSH injection (between 08.00 and 09.00 h) on cycle days 2 and 7 and then every other day. The last blood sample will be taken on the day of triggering regardless of the sampling frequency adopted. All blood samples will be centrifuged, and an aliquot will be stored at −20° until assayed.

#### 2.4.2. Endometrium Preparation

In recipients, there will be no fresh but only frozen/thawed embryo transfer. For this purpose, their endometrium will be prepared by administering hormone replacement therapy. The women will receive oral estradiol valerate as follows: 2 mg on cycle days 2–3, 4 mg on days 4–5 and 6 mg from day 6 onwards. Once the endometrium, at least 10 days after starting estradiol treatment, becomes thicker than 8 mm in diameter as assessed via a transvaginal ultrasound scan, micronized progesterone (Utrogestan caps 200 mg, Faran A.B.E.E., Athens, Greece) will be given vaginally at the daily dose of 400 mg (200 mg two times per day) or progesterone (Vasclor vag. Gel 8%, 22.5 G, Verisfield U.K. Ltd., Athens, Greece) once daily depending on the participating unit’s protocol. Estradiol valerate administration will continue at a dose of 4 mg per day. The maximum number of embryos to be transferred will be 2 per patient.

### 2.5. Intended Comparisons and Outcomes

The primary outcome measures will be the frequency of LH secretory peaks during the administration of the GnRH antagonist according to the adopted frequency of blood sampling. A secretory peak of LH is defined as the increase at levels ≥ 10 IU/L. Progesterone elevation > 1 ng/mL any time during the ovarian stimulation period will be also evaluated. Secondary outcome measures will be ongoing clinical pregnancy (fetal heartbeat at ultrasound) and miscarriage rates. Other prespecified outcome parameters included the total dose of gonadotropins (FSH), the endometrial thickness at day of triggering, number of retrieved cumulus oocytes complexes (COCs), MII oocytes, transferred embryos, day of embryo transfer, biochemical pregnancy (positive β-hCG), multiple pregnancy, ectopic pregnancy and live birth rates. Maternal side effects from the use of both drugs will also be monitored, including ovarian hyperstimulation syndrome. Embryo quality for embryo transfer or cryopreservation will be assessed according to morphological criteria [20].

Our primary analysis will be performed to provide a direct comparison of the study and control groups. We will also carry out logistic regression analysis, inserting variables, including demographic and IVF cycle characteristics, in order to reveal potential independent predictors that could potentially contribute to the change in the primary outcomes and live birth rate.

### 2.6. Calculation of Sample Size

The present trial will be based on a consecutive series of patients. The sample size will be calculated as follows: If there is a true difference in favor of the experimental treatment of 5% (20% vs. 15%), then 160 patients (80 per group in case of 1:1 enrollment) are required to be 80% sure that the upper limit of a one-sided 95% confidence interval (or equivalently a 90% two-sided confidence interval) will exclude a difference in favor of the standard/control group of more than 10%. According to a pre-decided pattern from all authors, a pilot study will proceed the full procedure; in that, a total of 50 study subjects will constitute the first cohort in a ratio of 1:1 in both groups.

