Despite the above-mentioned “weaknesses” of the GnRH antagonists, no significant difference in live birth rate has been shown between COH protocols for IVF using agonists and those using antagonists [12]. This could be interpreted as indicating that any premature rise in LH or even progesterone levels during COH is of negligible value for a successful final outcome. In other words, failure to administer a drug to block the LH surge in IVF cycles may not have a significant impact on the clinical outcome. Preliminary data have shown that it is possible to attempt an IVF treatment in fresh cycles without the use of a GnRH antagonist or any other medication to prevent a LH surge during COH [13]. It was interesting that women receiving a GnRH antagonist had LH levels during stimulation similar or even significantly higher than women without an antagonist [13]. To date, there is no information on this topic in the context of a prospective controlled trial. However, as the prevention of the LH surge is an established procedure in fresh cycles, the question is whether such a study can be performed in frozen cycles.

Recently, progesterone-primed protocols have been introduced in cycles with “freeze all” embryos [14]. The results have shown that the live birth rate following frozen/thawed embryo transfer does not differ significantly between protocols with progesterone and those with GnRH antagonists or agonists, while there is no difference in the congenital malformation risk either [15,16]. This could lead to the safe conclusion that, in the case of elective freezing, GnRH analogues are not necessary for LH surge prevention, while GnRH agonists could be used for triggering the final oocyte maturation. On the other hand, premature luteinization has been shown to reduce the chance of pregnancy in fresh but not in frozen cycles, thus suggesting that progesterone adversely affects the endometrium, which is not a concern in frozen cycles [17]. If so, then it is questionable whether exogenous progesterone is also necessary to prevent the LH surge in elective freezing cycles [18].

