The aim of this pilot study is to compare the efficacy of a protocol using FSH alone with that of a protocol using FSH plus a GnRH antagonist for COH in cycles of elective freezing in the context of a donor/recipient program. The hypothesis to be tested is that a COH protocol that includes FSH alone without any LH surge prevention regimens is not inferior to a protocol including FSH plus a GnRH antagonist in terms of clinical outcomes.

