Despite the fact that during ovarian stimulation with FSH the threshold for the positive feedback is exceeded early in the cycle, an endogenous LH surge has been reported in about 20% of stimulated cycles [2]. This relatively low incidence of a spontaneous LH surge during ovarian stimulation with FSH alone has been attributed to the overproduction by the ovaries of a substance named gonadotrophin surge-attenuating factor (GnSAF), which antagonizes the sensitizing effect of estradiol on the response of the pituitary to GnRH, thereby weakening or disabling the positive feedback mechanism [24,25,26]. Thus, GnSAF causes a marked attenuation or even complete blockade of the LH surge [27,28]. However, the inability to predict in which cycles a premature LH surge will occur during ovarian stimulation is the reason for the use of the relevant drugs in all women, although only about two in ten will benefit.

The rationale behind trying to prevent the LH surge during ovarian stimulation is to prevent the associated premature luteinization. Even a markedly attenuated LH surge can lead to premature luteinization [29]. Evidence has been provided that premature luteinization can cause advanced maturation of the endometrium or glandular–stromal dyssynchrony, which adversely affects the clinical outcome [30]. This would be the main obstacle to undertaking COH without GnRH analogues in fresh cycles. However, with the recent development of vitrification, which makes it possible to freeze all embryos with high success, this obstacle may be overcome. It is important to note that there is no consensus regarding the cut off level of serum progesterone that defines luteinization. Different studies have investigated the impact of various levels, from 0.8 ng/mL up to 3 ng/mL, on the clinical outcome during ART [17]. For the purpose of the present study, in cycles with a secretory LH peak, a progesterone cut off level will be considered the value of 1 ng/mL, as previously reported [4,5,6].

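### The non-inferiority hypothesis is about clinical outcome, the primary outcome is LH peaks, and the 160-patient calculation names no outcome, so its 80% power cannot be tied to either

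*Protocol article*

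**What the plan says.** Four parts of the protocol article bear on this point.

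- **Hypothesis** (Abstract; end of 1. Introduction): FSH alone "is not inferior to a protocol including FSH plus a GnRH antagonist in terms of clinical outcomes". The opening of the Discussion likewise expects an answer on clinical efficacy after frozen/thawed transfer.
- **Outcomes** (2.5): "The primary outcome measures will be the frequency of LH secretory peaks during the administration of the GnRH antagonist". Progesterone elevation is evaluated alongside. Clinical results rank lower: "Secondary outcome measures will be ongoing clinical pregnancy (fetal heartbeat at ultrasound) and miscarriage rates". Live birth is among the other parameters.
- **Sample size** (2.6): "If there is a true difference in favor of the experimental treatment of 5% (20% vs. 15%), then 160 patients", 80 per group, give 80% assurance that a one-sided 95% limit (equivalently a two-sided 90% interval) "will exclude a difference in favor of the standard/control group of more than 10" percentage points. A first cohort of 50, split 1:1, precedes the full study.
- **Analysis** (2.7): categorical variables are compared by chi-square and Fisher's exact test, and all tests are two-sided. No comparison with the 10-point margin is given.

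**The concern.** Hypothesis, primary outcome and sample size should describe one comparison. Here the first is clinical, the second hormonal, and the third is attached to nothing.

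LH peaks cannot simply stand in for clinical outcome. The Introduction itself suggests, as a possible interpretation, that "any premature rise in LH or even progesterone levels during COH is of negligible value for a successful final outcome". On that reasoning, more peaks on FSH alone would not refute the hypothesis, and equal peaks would not establish it.

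What is at stake is what the trial may conclude. While the endpoint behind the 160 is open, either the hormonal or a clinical result could later be presented as the powered non-inferiority comparison. A non-significant two-sided test could also be taken for non-inferiority, which it does not show.

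**Working it through.** **Inputs (2.6).** Rates 20% and 15%; true difference 5 points in favour of FSH alone; margin 10 points; one-sided 5% level (z = 1.645); power 80% (z = 0.842); 80 per group; first cohort 25 per group.

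**Formulas.** Let D be the true advantage of FSH alone, and V = pE(1 − pE) + pC(1 − pC), where E is FSH alone and C is control.
- n per group = (1.645 + 0.842)² × V / (D + 0.10)²
- power = Φ[(D + 0.10)/√(V/n) − 1.645]

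**1. The plan's own figure.** V = 0.20 × 0.80 + 0.15 × 0.85 = 0.2875 and D = 0.05.
- n = 2.487² × 0.2875 / 0.15² = 79.0 per group, or 158 in total against the stated 160.
- At 80 per group, √(0.2875/80) = 0.0599, and power = Φ(0.15/0.0599 − 1.645) = 80.4%.

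The stated figure is reproduced. At a one-sided 2.5% level it would be 101 per group, so the 5% level is the one used.

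**2. Does the figure identify the outcome?**

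| Reading | FSH alone | Control | D | V | n per group |
|---|---|---|---|---|---|
| Beneficial event | 20% | 15% | +0.05 | 0.2875 | 79 |
| Adverse event | 15% | 20% | +0.05 | 0.2875 | 79 |

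It does not. Both readings favour the experimental arm by 5 points and need the same number.

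**3. Power at 80 per group with no true difference (D = 0).**
- 15% in both groups: V = 0.255, √(V/80) = 0.0565, power = Φ(0.10/0.0565 − 1.645) = 55%.
- 20% in both groups: V = 0.32, √(V/80) = 0.0632, power = Φ(0.10/0.0632 − 1.645) = 47%.

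For scale, 80% power at no true difference would need 158 or 198 per group respectively.

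**4. First cohort, 25 per group, on the plan's own 5-point advantage.** √(0.2875/25) = 0.1072, and power = Φ(0.15/0.1072 − 1.645) = 40%.

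**5. Test against margin.** The calculation needs a confidence limit compared with a 10-point difference. A two-sided chi-square or Fisher test addresses a difference of zero, so the analysis in 2.7 is not the one for which 2.6 computes power.

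**The case against.** **What stands on the other side.** This stage is a pilot. Section 2.6 puts 50 subjects first, and the Discussion concedes that the study is observational, that no definite conclusion can be drawn, and that a proper randomised trial is the later aim. This lowers the weight of the point. Assuming a favourable true difference is also legitimate in a non-inferiority calculation: the margin defines the claim, and 2.6 discloses the assumption. The request for power at equality is therefore about transparency and does not correct an error.

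**Stronger readings that a reader might infer, and that the documents do not support.**

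- *The 20% and 15% must be pregnancy rates.* The article gives no pregnancy rate, and an adverse event at 15% against 20% yields the same number. Fewer LH peaks on FSH alone is conceivable here, since the Introduction cites peak rates of 8–35% under antagonist. The figures may even have been meant for LH peaks.
- *The 20% is the surge rate in the Discussion, so the difference runs against FSH alone.* The Discussion does say that "an endogenous LH surge has been reported in about 20% of stimulated cycles", but 2.6 cites no source and states the opposite direction. Pairing 20% on FSH alone with an assumed 15% on antagonist gives 21% power and 711 per group. An assumed 35%, also within the cited range, gives 97% power at 80 per group. These are illustrations and measure no defect in the plan.
- *The margin is missed even when the observed rates are equal.* At 20% in both groups the 90% half-width is 1.645 × 0.0632 = 10.4 points, so it is missed. At 15% in both it is 1.645 × 0.0565 = 9.3 points, so it is met.
- *An LH-peak result will be reported as clinical efficacy.* The text permits this but does not say it. Section 2.5 lists pregnancy outcomes separately.

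**Conclusion.** The point holds as a failure of alignment; the arithmetic is correct. As written, the plan has no powered test of its own hypothesis: the 80% cannot be tied to the declared primary outcome or to any clinical outcome, and the planned tests do not address the margin. Which endpoint was intended cannot be settled from the article.

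The 80% holds only if FSH alone is truly 5 points better. It falls to about 47–55% at no true difference, and is about 40% in the 50-subject cohort on the plan's own assumption. These figures assume a binary endpoint at the rates in 2.6, a one-sided 5% level and the normal approximation with unpooled variance. The point should be corrected before results are read. The pilot status and the authors' own caveat keep it from being critical at this stage.

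**What to change.** In 2.5 to 2.7:

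1. State which endpoint, which direction and which margin the 20%/15% and the 160 refer to, and make that endpoint the one that carries the non-inferiority claim. Only the sponsor can supply this.
2. If it is a clinical outcome, name it as the endpoint for that claim, and report LH peaks as a mechanistic outcome with a confidence interval. If it is LH peaks, reword the hypothesis so that no clinical non-inferiority is concluded from them.
3. Analyse the chosen endpoint by the two-sided 90% confidence interval for the difference, set against the 10-point margin. Keep the two-sided tests for the other comparisons.
4. Beside the 80%, give the power at zero true difference (about 47–55% with 80 per group), and say that the 50-subject cohort does not carry the 80%.

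The cost is protocol wording and a less favourable stated power. No extra patients are needed.
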